# Reno-protective effects of oral alkalizing agents in chronic kidney disease with aciduria: protocol for a randomized cohort study

**DOI:** 10.1186/s12882-020-01807-8

**Published:** 2020-04-22

**Keywords:** Chronic kidney disease, Oral alkalizing agents, Bicarbonate, Citrate, Single-centered and randomized cohort study

## Abstract

**Background:**

Aciduria caused by urinary excretion of acidic metabolic wastes produced in daily life is known to be augmented in patients with chronic kidney disease (CKD). To evaluate the reno-protective effect of oral alkalizing agents for the improvement of metabolic acidosis and neutralization of intratubular pH in the patients with mild stages of CKD. Also, to identify reno-protective surrogate markers in the serum and urine that can closely associate the effect of urine alkalization.

**Methods:**

In this single-centered, open-labeled, randomized cohort study, patients with CKD stages G2, G3a and G3b, who visited and were treated at Tohoku University Hospital during the enrollment period were registered. We administered sodium bicarbonate or sodium-potassium citrate as the oral alkalinizing agents. A total of 150 patients with CKD will be randomly allocated into the following three groups: sodium bicarbonate, sodium-potassium citrate and standard therapy group without any alkalinizing agents. The data of performance status, venous blood test, spot urine test, venous blood-gas test, electrocardiogram, renal arterial ultrasonography and chest X-ray will be collected at 0, 6, 12 and 24 weeks (short-term study) from starting the interventions. These data will be also collected at 1 and 2 years (long-term study). The samples of plasma and serum and early-morning urine at every visit will be acquired for the analysis of renal function and surrogate uremic biomarkers.

The recruitment for this cohort study terminated in March, 2018, and the follow-up period for all the enrolled subjects will be terminated in December, 2020. The primary endpoint will be the development of originally-defined significant renal dysfunction or the occurrence of any cerebrovascular disease in the short-term study. The secondary endpoint will be the same endpoints as in the long-term study, or the patients with significant changes in the suggested the surrogate biomarkers.

**Discussion:**

The findings of this study will address the importance of taking oral alkalizing agents in the patients with early stages of CKD, furthermore they could address any new surrogate biomarkers that can be useful from early stage CKD.

**Trial registration:**

Registered Report Identifier: UMIN000010059 and jRCT021180043.

The trial registration number; 150.

Date of registration; 2013/02/26.

## Background

Chronic kidney disease (CKD) is a chronic progressive disease related to eating habits and lifestyle [1–3]. These days, the increment of end-stage kidney disease (ESKD) is one of the biggest problems in the management of CKD patients [4]. If the patients with CKD are not properly treated, the disease may lead to cardiovascular events as well as ESKD and renal death [5, 6]. The treatment to ameliorate tubulo-interstitial dysfunction in the progression of CKD is important for preventing the final common pathway leading to ESKD [7, 8], which is yet to be verified by clinical research.

Generally, renal dysfunction may lead to metabolic acidosis and hyperkalemia, both derived from the accumulation of acidic metabolic wastes produced in daily life [9–11]. The acidic metabolic compounds, called uremic toxins (UTs), are the substances that primarily cause the aciduria [12, 13]. The accumulation of UTs is more common in CKD patients than in healthy individuals because of the disturbed urinary excretion from the damaged kidneys [14]. Some types of UTs are known to stimulate the ROS production, which may lead to further renal tubule-interstitial dysfunction [15, 16]. Physiological acidification in renal tubules is not harmful itself; however, we previously reported that a stronger acid condition in renal tubules could result in an increased production of reactive oxidative stress (ROS), which could be aggravated by albuminuria [17]. In this previous study with a CKD animal model, an oral alkalinizing agent also improved aciduria by neutralizing renal intratubular pH and alleviating the latent metabolic acidosis.

In several past reports, treatments with some alkalinizing agents (sodium bicarbonate and sodium citrate) ameliorated renal damage in CKD patients with eGFR < 60 ml/min/1.73m^2^ [18–20]. In addition, intake of fruits and vegetables also ameliorated the renal dysfunction and high blood pressure [21]. Oral alkalinizing agents are also suggested to be useful for prolonging the initiation of hemodialysis by some unknown mechanisms, but this possible effect is still to be scientifically established.

In this protocol report, we planned a single-center randomly-allocated cohort trial, entitled as “Estimating the efficacy of the Oral ALkalinizing Agents in CKD; *i.e.* CKOALA study (UMIN000010059)”, to verify the reno-protective effects of the oral alkalinizing agents in patients with mild stages of CKD, and also to seek renal protective surrogate markers, affected by the reno-tubular alkalization.

## Methods

### Aims

To verify the renal protective effects of oral alkalinizing agents by neutralizing the aciduria in the patients with mild stages of CKD.

## Objectives

Our objectives are as follows:
To confirm the protective effects of oral alkalinizing agents on renal function in patients with mild and moderate-stages of CKD.To compare the reno-protective effects of two types of oral alkalinizing agents, sodium/potassium citrate and sodium bicarbonate in CKD patients. Their effects will also be compared with that in the standard therapy group without oral alkalinizing agents.To seek for the new surrogate markers in the serum and urine associated with early renal damage that can be cancelled by oral alkalinizing agents.

### Overview of study design

This study is a single-center, open-label, randomly-allocated cohort study, with CKD patients in stages G2, G3a and G3b. To reduce the risk of sampling error, the enrolled patients will be randomly assigned based on the stratified random sampling process by using the random sequence generated by a computer software [22, 23]. The used variables for the stratification will be age (i.e. ≥65, < 65 years old), sex, presence of diabetes mellitus, and eGFR (i.e. ≥46, < 46 ml/min/1.73m^2^). With these four variables, the enrolled patients will be divided into 16 subgroups, and then randomly allocated into the below-described three cohort groups from each of the subgroups.

The enrolled patients will be allocated into the following three cohort groups: 1) sodium bicarbonate group, 2) sodium-potassium citrate group, and 3) standard therapy group without any alkalinizing agents. Then, these three cohort groups will be measured for the targeted biomarkers in the serum and urine in the “short-term” study (i.e. at 0, 6, 12 and 24 weeks after starting the intervention) and in the “long-term” study (i.e. at 1 and 2 years after starting the interventions) to assess the effects of oral alkalinizing agents. As for the urine samples, both early-morning urine and spot urine will be collected. The above-described overview of this cohort study is shown in Fig. 1.

**Fig. 1 Fig1:**
[figure not shown]
Overview of the CKOALA cohort study. Abbreviations: Cre, creatinine; eGFR, estimated glomerular filtration rate; gCr, gram adjusted by the urine creatinine level

### Collected variables

At the time of registration, written informed consent is acquired from all the enrolled patients. At this time, the following information as to the patient’s background are also collected: birthdate, sex, past medical history, complications, medication history, allergic history, smoking history, amount of alcohol intake, body weight and height.

The routine physical examinations, medication usage, and occurrence of adverse events are confirmed at every check-up in both the short-term and the long-term assessments.

Other data concerning the quality of life (QOL), laboratory test, chest X-ray, and physiological studies are confirmed at the set periods shown in Table 1. In detail, cardiac-thoracic ratio and presence of congestion for chest XRs, severe arrhythmia, angina pectoris and acute myocardial infarction for ECG and intrarenal blood flow and renal size for renal US. The QOL was assessed by using the SF-8™ Health Survey (Standard, Japanese version) by QualityMetric Incorporation and Shunichi Fukuhara (iHope international) [24]. The details of each blood test category and urine test category are listed in Table 2.

**Table 1 Tab1:** Items and timing of laboratory and physiological examinations for short-term and long-term assessments

	Short-term				Long-term	
	0 wk	6 wks	12 wks	24 wks	1 year	2 year
QOL (SF-8™)	○	–	–	○	–	–
Blood test						
Category I	○	○	○	○	○	○
Category II	○	–	–	○	△	△
Urine test						
Category I	○	○	○	○	○	○
Category II	○	○	○	○	△	△
ECG	○	–	–	○	○	○
CAVI, ABI	○	–	–	○	○	○
Renal US	○	–	–	○	○	○
Chest X-ray	○	–	–	○	○	○

Details of the categories I and II of both blood and urine tests are listed in the following Table 2. The circles show that the examinations will be performed at each time without exceptions. The triangles show that the examinations will be performed if the measured values in the short-term period showed abnormality and their follow-up is suggested to be desirable

**Table 2 Tab2:** Details of categories I and II of both blood and urine tests

**Category I (blood test)**	
Complete blood cell count, hemogram, hemoglobin, hematocrit, reticulocyte, Cre, eGFR, uric acid, Na^+^, K^+^, Cl^−^, IgG, HCO3^−^, total cholesterol, LDL-cholesterol, HDL-cholesterol, triglyceride, glucose, HbA1c, CRP, BUN, Ca^2+^, phosphate ion, magnesium ion, Fe, TIBC, UIBC, total protein, albumin, AST, ALT, LDH, ALP, transferrin, α1-microglobulin	
**Category II (blood test)**	
Ferritin, whole PTH, plasma renin concentration, plasma aldosterone concentration, BNP, erythropoietin, bone specific alkaline phosphatase (BAP), insulin, cortisol, ACTH, leptin, adiponectin, endothelin-1 (ET-1)	
**Category I (urine test)**	
Creatinine, protein, albumin, pH, Na, K, Cl, urobilinogen, bilirubin, ketone body, occult blood, urinary sediments	
**Category II (urine test)**	
IgG, transferrin, retino-binding protein (RBP), α1-microglobulin, α2-microglobulin, NAG, Neutrophil Gelatinase-Associated Lipocalin (NGAL), KIM-1, L-FABP, 8-isoprastan, 8-OHdG, type IV collagen, ET-1, angiotensinogen, MCP-1, thioredoxin, IL-1β, IL-6, TNF-α, aldosterone, HCO3^−^, lactate, pH	

### Eligibility criteria for participants

The patients, 20 to 80 years of age with CKD stages G2, G3a and G3b who were treated at Tohoku University Hospital between March, 2014 and March, 2018, will be eligible for this study. As for the exclusion criteria, patients who were administered with any medications or drinks that could have possible alkalinizing effects, or patients with tolvaptan within 30 days prior to the registration will be excluded. In addition, patients with renal hypouricemia, hyperkalemia, diabetes insipidus, hypernatremia with unknown origins, morning urinary pH higher than 6.8, or serious complications of heart disease or liver disease will also be excluded. Patients with hyperuricemia, morning aciduria, or metabolic acidosis will not be excluded.

### Drug intervention

Administration of each oral alkalizing agent, sodium/potassium citrate or sodium bicarbonate, is started at 1.5 g per day. When early-morning urine pH is under pH 6.5, the drug will be increased to 3.0 g per day. When early-morning urine pH is over pH 7.2, the drug will be decreased or ceased up to less than pH 6.8.

### Censoring criteria

The censoring criteria as following; 1. hypernatremia, lower leg edema or early morning urine pH 7.2 or higher for 2 months even after taking a drug holiday, 2. Serum potassium level keeps over 5.5 mEq/L or under 3.5 mEq/L, 3. Adverse events such as exacerbation of symptoms on heart, liver or kidney, 4. subjects found to be ineligible after starting protocol treatment, 5. subject who want to stop or withdrawal the consent, 6. Subjects who do not visit because of moving etc. Data of censored subjects will be excluded.

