### Endpoints

The primary endpoints will be **1)** the development of significant renal dysfunction, **2)** the occurrence of any kind of cerebrovascular disease between 0 and 24 weeks (short-term study) from starting the interventions. The significant renal dysfunction will be defined as the conditions that fulfill at least one of the following four criteria; 1. serum Cre level ≥ 1.5 times higher than that at 0 week, 2. eGFR decrease ≥20 ml/min/1.73m^2^ from that at 0 week, 3. proteinuria ≥3.5 g/gCr, 4. new development of urinary stones. The secondary endpoints will be the above-described criteria at 1 and 2 years (long-term study) from starting the interventions, and finding any kind of reno-protective marker associated with alkalinizing agents in both periods of study (Table 3).

**Table 3 Tab3:** Primary and Secondary Endpoints

Endpoints	Period	
Primary	Short-term	1) The development of significant renal dysfunction 1. serum Cre level ≥ 1.5 times higher than that at 0 week 2. eGFR decrease ≥20 ml/min/1.73m^2^ from that at 0 week 3. proteinuria ≥3.5 g/gCr 4. new development of urinary stones 2) The occurrence of any kind of CVD and the death
Secondary	Lon-term	1) The development of significant renal dysfunction 2) The occurrence of any kind of CVD and the death
	Short-term & Lon-term	Reno-protective marker associated with alkalinizing agents in both periods of study, for example, category II (blood tests), categoryII (urine test), urine pH and unknown surrogate biomarkers of early renal damage, including uremic toxins and known metabolites measured by metabolomics.

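### Excluding the data of every censored patient selects the analysed set on what happens after randomisation, and can remove primary events and harms, possibly unevenly by arm

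*Protocol article*

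**What the plan says.** Under Censoring criteria, the protocol article gives six reasons. The first is "hypernatremia, lower leg edema or early morning urine pH 7.2 or higher for 2 months even after taking a drug holiday". The second is "Serum potassium level keeps over 5.5 mEq/L or under 3.5 mEq/L". The third is "Adverse events such as exacerbation of symptoms on heart, liver or kidney". The fourth is ineligibility discovered after protocol treatment has started. The fifth and sixth are withdrawal and loss to follow-up. The section ends: "Data of censored subjects will be excluded". Nothing limits this to data collected after the censoring date.

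Under Endpoints, the primary endpoint over 0 to 24 weeks includes "the development of significant renal dysfunction", defined by creatinine, eGFR, proteinuria or new stones. The text adds cerebrovascular disease, and Table 3 words this part as "The occurrence of any kind of CVD and the death".

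Under Overview of study design, the third arm is a "standard therapy group without any alkalinizing agents". The same section says: "This study is a single-center, open-label, randomly-allocated cohort study". Under Analysis, dichotomous outcomes are compared by chi-squared or Fisher's exact test. No section says that all randomised patients are analysed as allocated, or that an endpoint event takes precedence over censoring.

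**The concern.** Three features of the rule act together.

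- **Overlap with the outcome.** A patient whose kidney disease worsens can meet the third reason and be removed because of the process that the trial measures. The heart part overlaps to the extent that CVD in Table 3 means cardiovascular disease, which the article does not spell out.
- **Dependence on treatment.** Controls take no study drug, so they cannot have a drug holiday. Eligibility criteria exclude a morning urine pH above 6.8 at entry, and the treated arms are titrated on urine pH. A sustained pH of 7.2 or more is therefore in practice a feature of the alkali arms.
- **Room for judgement.** The third reason is open-ended, and the fourth is applied after treatment has started with the arm known. The Discussion sets open-label bias aside because the endpoints are objectively measured. That does not cover the decision about who is excluded.

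At stake is the randomised comparison itself, for the primary endpoint, for the same endpoints at 1 and 2 years, and for harms that led to censoring.

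**Working it through.** **1. Could the word censoring rescue the rule?** Ending follow-up at the censoring date would need a method that uses partial follow-up. The Analysis section gives ANOVA or Kruskal-Wallis, paired tests, chi-squared or Fisher tests, and correlations. None of these uses partial follow-up, so exclusion is the plain reading.

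**2. Effect on observed risks when there is no true effect.** Let p be the true risk in both arms, f the share of event patients excluded and g the share of non-event patients excluded. Then

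observed risk = p(1−f) / [p(1−f) + (1−p)(1−g)].

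The article gives no p, f or g for this purpose, so all three are assumptions. With p = 0.20:

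- f = 0.5, g = 0: 0.10/(0.10+0.80) = 11.1%
- f = 0.2, g = 0: 0.16/(0.16+0.80) = 16.7%
- f = 0.3, g = 0: 0.14/(0.14+0.80) = 14.9%
- f = 0, g = 0.2: 0.20/(0.20+0.64) = 23.8%

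With p = 0.05, f = 0.5, g = 0: 0.025/(0.025+0.95) = 2.6%.

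False-positive rates come from simulating one alkali arm against control, 50 randomised per arm, with an uncorrected two-sided chi-squared test:

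| True risk | Excluded | Alkali vs control | p<0.05 | p<0.01 |
|---|---|---|---|---|
| 20% | nobody | 20% vs 20% | about 5% | about 1% |
| 20% | events: half alkali, no control | 11% vs 20% | 22% | 7% |
| 20% | events: half alkali, one-fifth control | 11% vs 17% | 12% | 3% |
| 20% | events: 30% in each arm | 15% vs 15% | about 5% | about 1% |
| 20% | non-events: 20% alkali only | 24% vs 20% (against alkali) | 7% | 2% |
| 20% | events: one-fifth alkali, half control | 17% vs 11% (against alkali) | 12% | 3% |
| 5% | events: half alkali, no control | 2.6% vs 5% | 7% | 0.4% |

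**3. Effect on power.** The plan's own figure comes first. Sample size calculation gives 5% and 30%, alpha 0.05, power 80% and 50 per group. The text attaches these two rates to the two alkali groups; that is a separate matter, and they are used here only as planning rates. Taking alpha as two-sided:

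n = [1.96·√(2·0.175·0.825) + 0.8416·√(0.05·0.95 + 0.30·0.70)]² / 0.25² = (1.053 + 0.427)² / 0.0625 = 35.1, so 36 per arm, or 43 with continuity correction.

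The stated 50 is not reproduced, but it exceeds what its inputs require. Exact binomial enumeration at 5% versus 30% gives:

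| Per arm | Chi-squared, 0.05 | Fisher, 0.05 | Chi-squared, 0.01 | Fisher, 0.01 |
|---|---|---|---|---|
| 50 | 95% | 90% | 82% | 75% |
| 40 (20% lost) | 89% | 82% | 70% | 57% |

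This treats the loss as unrelated to outcome. If exclusion falls on events equally in both arms, the normal approximation at alpha 0.05 goes from 92% with no loss to 84%, 68% or 43% when 25%, 50% or 75% of events are removed.

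**The case against.** A reader might infer more than the documents support, in four ways.

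- **That the rule does remove events unevenly and favours alkali.** The third reason covers all three arms, and nothing shows how often it would apply in each. Equal deletion leaves the error rate at about 5%, and some patterns work against alkali. Of the listed reasons, only the drug-holiday pH item is clearly arm-specific. Hypernatremia and edema can occur in controls. The Background attributes hyperkalemia to renal dysfunction, so the potassium limits may remove worsening patients in any arm.
- **That the trial becomes underpowered.** At the planning alpha of 0.05, a 20% loss unrelated to outcome still leaves more than 80% power. The fall to 70% or 57% appears only if the 0.01 threshold applies to this comparison. The Analysis section states that threshold after the ANOVA and Kruskal-Wallis sentences and before the one on dichotomous data, so its reach is a matter of interpretation.
- **That harms will go unreported.** Adverse events are checked at every visit under Collected variables, and no section says that safety reporting uses the restricted set. Their loss from the comparison follows from the plain reading of the sentence but is not stated.
- **That all data before censoring are certainly discarded.** This too is the plain reading, not the literal text.

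These objections limit what can be said about size and direction. They leave the main point standing: the article states the rule outright, so it is not a detail left to an unseen analysis plan, and the rule selects patients on outcomes arising after randomisation.

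**Conclusion.** The point holds in this form. The exclusion rule as written makes the analysed set depend on post-randomisation outcomes, some of which overlap the primary endpoint and at least one of which is in practice confined to the alkali arms. Primary events and harms can be removed, possibly unevenly.

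The size and direction of the bias are not known from the document. Under assumed exclusion shares with no true effect, the false-positive rate at p<0.05 runs from about 5% (equal deletion) to 22% (half of alkali events, no control events, 20% risk). At 5% risk the latter pattern gives only about 7%. Loss of power is secondary and, at alpha 0.05, does not by itself defeat the plan unless exclusion falls heavily on events. The rule should be changed before analysis because it affects every comparison and the correction is cheap.

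**What to change.** Replace the closing sentence of Censoring criteria with wording such as:

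> All randomised patients are analysed in the arm to which they were allocated, using all available data, including events and laboratory values before and after stopping study treatment, subject to consent. Meeting any of criteria 1 to 4 does not remove a patient from the analysis. Patients who withdraw or are lost contribute data up to that date, with a sensitivity analysis for missing 24-week status. All adverse events are reported by allocated arm.

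Keep the set without censored patients only as a sensitivity analysis. What the criteria mean for study treatment need not change.

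Recruitment ended in March 2018 and the article appeared in April 2020, so the 24-week window had passed. For the primary endpoint, the sponsor can only retrieve whatever hospital data exist on patients who stopped; how complete those are is not stated. Follow-up can continue where 1- and 2-year visits are still open before the planned end in December 2020.

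The cost is a change of analysis wording and some record retrieval. The apparent effect may become smaller.

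### Stopping criteria met after randomisation also remove the patient's data, so the outcome comparison is not between the groups as randomised

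*Protocol article*

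**What the plan says.** The Censoring criteria section of the protocol article gives six items.

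- Item 1: "hypernatremia, lower leg edema or early morning urine pH 7.2 or higher for 2 months even after taking a drug holiday".
- Item 2: "Serum potassium level keeps over 5.5 mEq/L or under 3.5 mEq/L".
- Item 3: adverse events in which heart, liver or kidney symptoms worsen.
- Items 4 to 6: ineligibility discovered after treatment began, withdrawal, and loss to follow-up.

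The section closes with "Data of censored subjects will be excluded", which applies to all six. It does not say whether all of a patient's data go or only those after censoring.

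Four other sections bear on this:
- Eligibility excludes "morning urinary pH higher than 6.8" and also "patients with renal hypouricemia, hyperkalemia, diabetes insipidus, hypernatremia with unknown origins".
- Drug intervention starts each agent at 1.5 g per day, doubles it when morning pH is under 6.5, and provides: "When early-morning urine pH is over pH 7.2, the drug will be decreased or ceased". The standard therapy group has no agent to titrate or pause.
- Endpoints defines significant renal dysfunction by creatinine, eGFR, proteinuria or urinary stones over 24 weeks, and adds vascular events.
- Analysis compares event frequencies between groups by chi-squared or Fisher's exact test. The article names no analysis set and does not provide for following patients who stop drug.

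**The concern.** Rules for stopping a drug protect patients. Removing the data of those who stop is a separate decision, and here it is made on events that occur after allocation. Two features make that risky.

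First, item 3 overlaps the outcome. A patient whose kidney function is failing can meet item 3 and the renal endpoint through the same deterioration, and the exclusion sentence can then take that event out of the count. High potassium in item 2 has a weaker link of the same kind. Hyperkalemia is barred at entry, and the Background says that "renal dysfunction may lead to metabolic acidosis and hyperkalemia".

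Second, items 1 and 2 plausibly fire at different rates by arm. Both agents supply sodium, only the citrate supplies potassium, and only the drug arms are pushed towards a higher urine pH from an entry value of at most 6.8.

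A test of two proportions takes no account of censoring. If whole patients are deleted, the arms no longer have the balance that randomisation gave them. If only later data are deleted and the patient stays in the denominator, later events go uncounted, and the arm with more censoring looks better even at equal risk.

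**Working it through.** The plan gives no figure for censoring or its effect, so there is none to reproduce. The 50 per group does not enter the argument except as the arm size.

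**Inputs.** From the documents: 50 per group and alpha 0.05 (Sample size calculation), and the p < 0.01 threshold (Analysis). Assumed, because the documents are silent:
- share of one arm removed, f = 10% or 20%;
- risk of removed patients relative to those kept, k = 2 or 3;
- overall event risk, R = 5% or 20%;
- no true effect, and no removal in the standard arm.

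**All data of the patient removed.** Risk among those kept: r0 = R / (1 − f + f·k). Spurious difference = R − r0. For R = 20%, f = 0.10, k = 2: r0 = 0.20 / 1.10 = 18.2%, a difference of 1.8 points. Type I error comes from exact binomial enumeration of the uncorrected two-sided chi-squared test, 50 patients at risk R against 45 or 40 at risk r0.

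| f, k | Difference, R = 5% | Type I at 0.05, R = 5% | Difference, R = 20% | Type I at 0.05, R = 20% | Type I at 0.01, R = 20% |
|---|---|---|---|---|---|
| none | 0 | 4.3% | 0 | 5.2% | 1.0% |
| 10%, 2 | 0.5 | 3.1% | 1.8 | 5.6% | 1.0% |
| 10%, 3 | 0.8 | 3.0% | 3.3 | 7.0% | 1.4% |
| 20%, 2 | 0.8 | 4.3% | 3.3 | 6.4% | 1.4% |
| 20%, 3 | 1.4 | 4.1% | 5.7 | 10.0% | 2.5% |

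Differences are in percentage points. If removal is unrelated to risk (k = 1), the difference is 0.

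**Only later data removed, patient kept in the denominator.** Assume that half of the removed patients' events fall after censoring. Spurious difference = 0.5·f·k·r0. At R = 20%, for f = 10% and 20%: 1.0 and 2.0 points at k = 1, 1.8 and 3.3 at k = 2, 2.5 and 4.3 at k = 3. Under this reading a difference arises even when k = 1.

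**Price of keeping everyone.** Take the planning rates of 5% and 30% as alkali against comparator, and let a share f of the alkali arm stay in the analysis off drug at the 30% risk. The arm's risk is 0.05(1 − f) + 0.30f, that is 6.25%, 7.5% and 10% for f = 5%, 10% and 20%. With 50 per arm and alpha 0.05, power by normal approximation is 88%, 83% and 71% (exact enumeration: 91%, 86% and 73%). Deleting these patients gives a nominal 91%, 90% and 88% by normal approximation, but only if deletion causes no bias.

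**The case against.** **The pH trigger is narrow.** The drug is already cut or stopped above 7.2, and item 1 asks for a high pH that lasts two months despite a drug holiday. Reaching 7.2 is mainly a drug effect, but staying there off drug is less clearly one. The holiday condition may also qualify hypernatremia and edema, and those and the potassium limits can be met in any arm. This stands: different rates by arm are an inference from what the drugs contain and how they are titrated, and are not documented.

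**The effect may be negligible.** At 5% event risk there is no type I inflation, and at alpha 0.01 the error stays at 2.5% or less in the scenarios shown (whether that threshold covers the dichotomous tests is unclear). This also stands, and it limits the point's weight. It does not make the exclusion harmless at higher event rates.

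**Stronger readings that the documents do not support:**
- A reader might infer that the rule favours the alkali arms. Removing high-risk patients from a drug arm would flatter it, but removing progressing patients from the standard arm would hide a benefit. The text cannot settle which dominates.
- A reader might take 30% as the event risk, which with 20% removed at triple risk gives r0 = 0.30 / 1.40 = 21.4% and type I error of 14.5%. The planning rates are ESKD incidences based on a previous study, not rates of this 24-week endpoint.
- A reader might add that low potassium, edema or hypernatremia of known cause already present at week 0 could trigger removal, and ask for tighter entry criteria. Such conditions precede allocation and are balanced in expectation, so they do not support the point.

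**An unseen analysis plan could soften the rule.** It could, but the article states the exclusion outright and nothing in it overrides that sentence.

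**Conclusion.** The point holds: the article converts stopping criteria met after randomisation into a data-exclusion rule. Item 3 can remove patients on their way to the primary endpoint, and items 1 and 2 plausibly remove different numbers by arm. The comparison in the Analysis section is then not between the groups as randomised, whichever way the exclusion is read.

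The size and direction of the bias cannot be determined. The ranges in the brief assume that all of a patient's data are removed, from one arm only and at raised risk. One-sided removal makes them upper bounds for the given share and risk ratio. The sponsor should make the change, but the documents do not show that the result will be wrong.

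**What to change.** Replace the exclusion sentence as follows.

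- Items 1 to 3 are reasons to stop study drug only. Scheduled visits continue, and all available data are analysed in the randomised arm.
- For items 5 and 6, data up to withdrawal or loss are kept, where consent allows.
- An analysis that leaves out censored patients may stay as a sensitivity analysis.

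Item 4 is a separate matter. The entry criteria need no change.

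Timing matters. Recruitment ended in March 2018, so if treatment began at enrolment the last 24-week visit fell about September 2018. For the primary endpoint the change therefore means keeping data already collected and, where available and permitted, recovering values from routine care. For the 1- and 2-year endpoints, visits can continue until follow-up ends in December 2020.

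The cost is a wording change plus completing visits that are already scheduled for patients who stop drug. These include blood and urine tests, ECG, CAVI/ABI, renal ultrasound and chest X-ray. No new type of measurement is needed, and the article already provides that "The routine physical examinations, medication usage, and occurrence of adverse events are confirmed at every check-up". The statistical price is the dilution shown in the working, which is modest unless many patients stop drug.
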